**Fig. 2 Fig2:**
[figure not shown]
N1–N6 are 6 nights of intervention with zopiclone/placebo. The initial dose is zopiclone/placebo 3.75 mg (dose level 1). Dose level 2 is 5 mg zopiclone/placebo, and dose level 3 is 7.5 mg zopiclone/placebo

### Withdrawal criteria

Patients may withdraw from the trial at any time at their own request. Patients can be withdrawn from the study at the discretion of the treating physician if they have an acute complication of the cancer or the treatment, including sudden changes in their clinical condition such as cardiovascular events or sepsis.

### Data collection and statistics

The following variables will be recorded in the web-based case report form, which is administered by the Unit for Applied Clinical Research, (NTNU): date of birth, weight, height, concomitant diseases, psychiatric history, department category (i.e., palliative care unit or general oncology ward), principal cancer diagnosis (International Classification of Diseases (ICD-10)), date of the principal cancer diagnosis, site of metastases (bone, liver, lung, central nervous system, other), present anticancer treatment, and medications taken in the last 24 h. The Karnofsky Performance Status (KPS) scale will be used to assess performance status [34]. In addition, history and duration of opioid consumption will be obtained. Clinical chemistry results (hemoglobin, creatinine, C-reactive protein, albumin, and bilirubin) will be obtained from the medical record. Results collected less than 7 days before inclusion are considered valid.

The following populations will be considered for the analyses: (1) intention-to-treat population: all randomized patients regardless of protocol adherence; (2) per-protocol population: includes all subjects who have completed the study medication. A safety analysis will be performed, which includes all subjects who have received at least one dose of study medication. Subjects who withdraw from the study will be included in the safety analysis. The main statistical analysis will be performed when the target number of 100 patients has been recruited. Baseline characteristics will be summarized by mean and standard deviations (SDs) for continuous variables, and counts and percentages for categorical variables. The 11-point NRS for sleep quality is regarded as continuous. Comparison of means will be performed with the Student’s *t* test for continuous variables. The study follows the Consolidated Standards of Reporting Trials (CONSORT) recommendations for reporting RCTs. A *p* value of ≤0.05 will be considered statistically significant when comparing the two groups for the primary endpoint or the two secondary endpoints. Statistical analyses will be performed with SPSS version 25, IBM Statistics, Chicago, IL, USA.

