### Study objectives and endpoints

The primary objective is to study the short-time effectiveness of zopiclone on patient-reported subjective sleep quality in patients with advanced cancer who report insomnia. The primary endpoint is patient-reported sleep quality during the final study night with treatment (night 6) assessed on a numerical rating scale (NRS) of 0–10, where 0 = Best sleep and 10 = Worst possible sleep. The secondary objective is to study the effectiveness of zopiclone on mean self-reported total sleep time and sleep onset latency. Table 1 summarizes the objectives and endpoints including the explorative objectives.

**Table 1 Tab1:** Primary, secondary, and explorative objectives and related endpoints and assessments

	Objective	Endpoint	Assessment method
Primary	To study the short-time effectiveness of zopiclone on patient-reported subjective sleep quality	Patient-reported sleep quality the last study night (night 6)	Numerical rating scale 0–10, 0 = Best sleep, 10 = Worst possible sleep
Secondary	To study the short-time effectiveness of zopiclone on patient-reported TST	Patient-reported TST (minutes) the last study night (night 6)	Sleep diary
	To study the short-time effectiveness of zopiclone on patient-reported SOL	Patient-reported SOL (minutes) the last study night (night 6)	Sleep diary
Explorative	To study the short-time effectiveness of zopiclone on overall patient-reported sleep quality	Patient-reported overall sleep quality over a week time interval	Pittsburgh Sleep Quality Index
	To study the short-time effectiveness of zopiclone on objectively measured TST, SOL, SE, WASO, and NWAK	TST (minutes), SOL (minutes), SE (percent), WASO and NWAK during the last study night (night 6)	Actigraphy
	To study the short-time effectiveness of zopiclone on patient-reported TST, SOL, SE, WASO, and NWAK	TST (minutes), SOL (minutes), SE (percent), WASO, and NWAK during the last study night (night 6)	Sleep diary
	To study the short-time effectiveness of zopiclone on self-reported daytime sleepiness	Daytime sleepiness in the morning after night 6	Karolinska Sleepiness Scale

*TST* total sleep time, *SOL* sleep onset latency, *SE* sleep efficiency, *WASO* wake after sleep onset, *NWAK* number of awakenings

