### Sample size

The primary variable used in the sample size calculation is patient-reported sleep quality on an NRS of 0–10 during night 6 (the last study night with treatment). The defined minimal clinical important difference (MCID) between the two study groups (zopiclone/placebo) is 2 for the primary outcome sleep quality, scored on the NRS. Due to the lack of relevant data for MCID for NRS on sleep quality, this number was chosen based upon NRS in cancer pain studies [25, 26]. Data obtained in recent studies suggest an expected standard deviation of 2.75 [27–33]. Using a significance level of 5%, these assumptions indicate that for 80% power 33 patients are needed in each group. For 90% power a sample size of 42 per group is required. The study will aim for a 90% power and allow for an expected number of 8 drop-outs during the study period (6 nights). The study will include 50 patients in each treatment arm.

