### Treatment

The treatment is 6 subsequent nights with zopiclone or placebo. For this study, zopiclone “Actavis” 3.75 mg, 5 mg, and 7.5 mg (active comparator) are defined as the IMP. Kragerø Tablettproduksjon AS, Kragerø, Norway will produce, blind, pack, and label the IMP. Patients will receive the IMP in custom-made capsules containing zopiclone Actavis 3.75 mg, 5 mg, or 7.5 mg or placebo administered once daily (taken in the evening 30 min before going to bed). Each patient will receive six boxes, with each box containing the allocated IMP for 2 nights. Each box is labeled with dose level according to the titration. The initial dose of zopiclone/placebo is 3.75 mg/day started after 1 night with sleep quality assessment and symptom assessment. The study personnel will evaluate the patient by phone after 2 and 4 nights of being on study medication by asking the question “Please circle the number that best describes how you feel now” on an NRS, where 0 = Best sleep and 10 = Worst possible sleep. If the NRS value is ≥4 at evaluation (Fig. 2), the dose of zopiclone/placebo is increased one dose level according to dose level 1 = 3.75 mg zopiclone/placebo; dose level 2 = 5 mg zopiclone/placebo; dose level 3 = 7.5 mg zopiclone/placebo. If NRS is < 4 at evaluation, the patient continues on the same dose level. If patients titrated to dose level 2 at night 4 experience excess sedation during the daytime, the dose can be decreased to dose level 1 for nights 5 and 6. The patients will indicate in the sleep diary whether they have taken their trial drug or not and state the reason, given by the alternatives forgotten, side effects, or other, if they omitted the trial medication. Each patient will be instructed to contact the investigator immediately should they manifest any signs or symptoms they perceive as serious. End-of-protocol therapy is defined as therapy after 6 nights with treatment. Further treatment is the responsibility of the physician in charge of patient treatment. The protocol was considered as a low-risk study, and according to Norwegian legislations, a data monitoring committee was not needed.

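### As stated, the night-6 t test implies use only of patients with a night-6 score; up to 16% per arm may lack one, and no primary analysis set is named

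*Protocol article*

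**What the plan says.** All references are to the protocol article.

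- **Endpoint** (Study objectives and endpoints): "The primary endpoint is patient-reported sleep quality during the final study night with treatment (night 6"), scored 0 to 10 with 10 the worst.
- **Analysis sets** (Data collection and statistics): "intention-to-treat population: all randomized patients regardless of protocol adherence", and "per-protocol population: includes all subjects who have completed the study medication". Both are listed as populations to be considered. Neither is assigned to the primary comparison.
- **Test** (same section): "Comparison of means will be performed with the Student’s *t* test for continuous variables". No covariate and no model using other nights is named.
- **Drop-out** (Sample size): 42 per group are required for 90% power, and the trial will "allow for an expected number of 8 drop-outs during the study period (6 nights"), giving 50 per arm.
- **Earlier scores** (Treatment): sleep quality is assessed on one night before treatment starts, and "The study personnel will evaluate the patient by phone after 2 and 4 nights of being on study medication", with a 0 to 10 rating that guides titration.
- **Missed capsules** (Treatment): patients record omitted doses and the reason in the sleep diary.

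**The concern.** A t test on a single-night score, with nothing filled in, leaves out every patient without that score. The drop-out allowance fits this reading, because the 8 extra patients per arm are treated as adding nothing to the primary comparison. The likely result is a comparison of patients with observed scores, placed beside a set that is meant to hold everyone randomized.

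Enrolling extra patients protects power. It does not protect the comparison if those who leave differ from those who stay, and differ by arm. The article gives reasons to expect informative loss. Withdrawal may be at the patient's request or follow an acute complication, and daytime sedation and side effects are anticipated. At stake is a shift in the estimated difference that more patients cannot remove, while scores from earlier nights, which could reduce it, have no stated role in the analysis.

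**Working it through.** **1. The plan's own figure.** Inputs from Sample size: difference 2, SD 2.75, "Using a significance level of 5"%. Two-sided testing is assumed, because one-sided gives 33 at 90% power and does not fit.

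n per group = 2 × (SD/difference)² × (z for alpha + z for power)²

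- 90% power: 2 × (2.75/2)² × (1.960 + 1.282)² = 39.7, so 40. The exact t calculation gives 41; stated 42.
- 80% power: 29.7, so 30. Exact 31; stated 33.

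The stated figures are close and slightly generous. Exact power is 90.9% with 42 observed per arm and 94.9% with 50.

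**2. Expected loss.** 42 + 8 = 50, so the 8 is read as per arm: 8/50 = 16%. If it meant 8 in the whole trial, the share would be 8/100 = 8%.

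**3. Bias formula.** Let f be the share lost in an arm, and g the mean night-6 score of those lost minus that of those observed. The observed mean equals the full mean minus f × g. With benefit defined as placebo mean minus zopiclone mean:

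bias in benefit = f(zopiclone) × g(zopiclone) − f(placebo) × g(placebo)

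A positive value overstates the benefit of zopiclone. The documents give no values for g, so the following are assumed:

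| Lost, zopiclone / placebo | g, zopiclone / placebo | Bias |
|---|---|---|
| 16% / 16% | 2 / 2 | 0 |
| 16% / 8% | 2 / 2 | +0.16 |
| 16% / 16% | 2 / 0 | +0.32 |
| 16% / 16% | 2 / −2 | +0.64 |
| 16% / 16% | −2 / 2 | −0.64 |

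The last two rows are extremes, with opposite selection in the two arms.

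**4. A less arbitrary g.** Assume that loss depends on the night-4 score (logistic, slope 1.2 per SD), and that scores on different nights correlate 0.4 to 0.6. At 16% loss, those lost are about 1.0 SD (2.76 points) worse on night 4. At night 6 the gap is 0.4 to 0.6 × 2.76 = 1.10 to 1.66 points, so f × g = 0.16 × 1.10 to 0.16 × 1.66 = 0.18 to 0.26. Simulations with a true difference of 2 and 50 per arm, under assumptions of this kind, agree:

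| Assumed loss, zopiclone / placebo | Bias in benefit |
|---|---|
| 16% score-driven / 4% | +0.18 to +0.28 |
| 16% / 8%, both score-driven | +0.08 to +0.15 |
| 16% / 16%, same mechanism | about 0 |
| 4% / 18%, score-driven on placebo | −0.19 to −0.30 |
| zopiclone loss among better sleepers | −0.17 to −0.26 |

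Regression on the earlier scores brings the bias to about 0. That follows from the set-up, because loss was made to depend only on an observed score.

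**5. Effect on the test.** With 42 per arm and no true difference, a shift of 0.16 raises the two-sided rejection rate from 5% to 5.8%, and a shift of 0.32 raises it to 8.2%.

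**The case against.** The strongest reply is that the article never says scores will go unanalysed. It is silent on missing night-6 values, which is commonly left to an analysis plan that is not shown, and a t test can be run on imputed data. Adding 8 to 42 is a routine power allowance and does not fix how drop-outs are handled. This stands against any claim of contradiction. It does not dispose of the point, because the article does fix the single-night endpoint and the unadjusted test, and those two lead to an observed-scores comparison unless something is added.

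Three stronger readings are tempting and not supported:

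- **That the primary result is a complete-case analysis mislabelled as ITT.** The article does not name ITT as primary, so there is no such label to contradict.
- **That the per-protocol set has the same selection.** It selects on completed medication, not on having a score. A patient who skips a capsule and still fills in the diary belongs to ITT but may fall outside per-protocol.
- **That any response-related drop-out biases the result, in favor of zopiclone.** Equal loss by the same mechanism in both arms gives no bias in the difference. Heavier loss of poor responders on placebo would understate the benefit.

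It is also fair to doubt that the telephone scores are ready for use. The question asks how the patient feels at that moment, although its scale ends refer to sleep, and the article does not show that it matches the night-6 item.

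**Conclusion.** The point holds in limited form. As stated, the primary comparison implies use only of patients with a night-6 score, the design allows for up to 16% per arm without one, and no primary set is named. If loss depends on response or tolerability differently by arm, the bias under the assumed inputs is about 0.1 to 0.3 NRS points in either direction, roughly 5% to 15% of the difference of 2. It is about 0 when share and mechanism are equal.

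These sizes rest on assumed drop-out patterns and between-night correlations; the documents supply only the SD, the target difference and the count of 8. An unseen analysis plan may already settle the matter. The risk is modest and does not undermine the design, but it is cheap to reduce.

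**What to change.** Before unblinding, change the analysis wording as follows.

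1. Name ITT as the primary set and treat the per-protocol analysis as supportive.
2. Replace the unadjusted t test with a likelihood-based repeated-measures model of the sleep-quality NRS, adjusted for pre-treatment NRS and center, with the night-6 treatment contrast as the primary estimate.
3. Include the night-2 and night-4 scores as outcomes only after confirming that they use the endpoint item. Otherwise, fit a baseline-adjusted night-6 model with multiple imputation, using the earlier scores as auxiliary variables.
4. Use the night-6 score of every patient who still reports, whether or not capsules were taken.
5. Add one delta-adjusted sensitivity analysis, in which patients without a night-6 score are assumed to differ by a stated amount from what the model predicts.

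The cost is wording only: the pre-treatment and telephone ratings are already part of the procedures, and the sample size need not change. The small downside is that the primary model rests on a missing-at-random assumption, which step 5 tests.

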### Patient-reported outcome measures

#### The European Association for Palliative Care (EAPC) basic dataset

This questionnaire includes assessment of symptoms such as pain, tiredness, drowsiness, nausea, lack of appetite, shortness of breath, depression, anxiety, wellbeing, sleep, constipation, and vomiting [35]. Patient-reported sleep quality is assessed on an NRS of 0–10, where 0 = Best sleep and 10 = Worst possible sleep.

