### Objective measure of sleep

*Actigraphy* is a method of assessment that distinguishes between wakefulness and sleep from the presence or absence of limb movement [44]. The Actiwatch is a small wristwatch-sized device which is used to assess sleep-wake cycles [45]. It has been demonstrated that actigraphy sleep measures are sensitive enough to detect changes related to drug interventions [45]. In this trial, Actiwatch 2 (Philips Respironics, Inc., Murrysville, PA, USA) will be used to collect actigraphy data. Sleep will be measured in one night without study treatment, and then the actigraphy will monitor sleep continuously during the 6 nights in the treatment period (nights 1–6). Data will be analyzed with Actiwatch Spectrum and the latest version of Actiware software. The medium sensitivity setting will be used with an epoch length (i.e., the period of time that the actigraphy data is averaged) of 30 s [46].

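### The primary analysis is an unadjusted Student's t test of night-6 sleep quality, although a pre-treatment sleep-quality score is collected and could be used as a covariate

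*Protocol article*

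**What the plan says.** The Study objectives and endpoints section makes the primary outcome a single post-treatment value, not a change score: "The primary endpoint is patient-reported sleep quality during the final study night with treatment (night 6) assessed on a numerical rating scale (NRS) of 0–10". Data collection and statistics then says "The 11-point NRS for sleep quality is regarded as continuous", and the next sentence gives the method: "Comparison of means will be performed with the Student’s *t* test for continuous variables". No other test, covariate, change score or centre term appears in the article.

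A pre-treatment value is planned. In the Treatment section the first dose is "started after 1 night with sleep quality assessment and symptom assessment". The symptom questionnaire, described under the EAPC basic dataset, uses the same scale as the primary endpoint: "Patient-reported sleep quality is assessed on an NRS of 0–10, where 0 = Best sleep and 10 = Worst possible sleep". For actigraphy, Objective measure of sleep adds "Sleep will be measured in one night without study treatment".

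Randomisation is stratified by study centre only. The inclusion criteria ask for insomnia symptoms, their frequency and daytime impairment, but set no minimum sleep-quality score.

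**The concern.** A patient's sleep quality before treatment will usually predict the same patient's sleep quality a week later to some degree. In an unadjusted comparison that predictable part of the between-patient variation stays in the error term. The standard error and confidence interval are then wider than the data require.

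The design does not balance baseline sleep quality between the arms, because only centre is a stratification factor. If one arm happens to start with worse sleepers, part of that difference passes into the observed treatment effect. Over repeated randomisations this is the same variance as in the previous paragraph and is already in the t test's standard error. In the single trial that will be run, however, it makes the estimate harder to interpret.

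Precision matters here for two reasons. The 2-point target was borrowed from cancer pain studies because sleep data were lacking, so a smaller true effect is plausible. The Discussion also describes recruitment of these patients as a major challenge.

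**Working it through.** **Inputs from the protocol article**
- Target difference, from Sample size: "The defined minimal clinical important difference (MCID) between the two study groups (zopiclone/placebo) is 2 for the primary outcome sleep quality".
- SD, from Sample size: "Data obtained in recent studies suggest an expected standard deviation of 2.75".
- Significance level 5%. Sidedness is not stated; two-sided is assumed, because one-sided gives 33 per group at 90% power, which does not fit the stated 42.
- 42 per group for 90% power, 33 for 80%; 50 randomised per arm.

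**Assumptions not in the article**
- r, the correlation between the pre-treatment and night-6 scores. The range 0.1 to 0.6 is shown.
- Baseline SD equal to 2.75, used only in the imbalance calculation.

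**Step 1. Reproduce the stated sample size.** For an unadjusted two-sided comparison of two means with difference 2 and SD 2.75, the normal approximation gives 40 per group at 90% power. The exact noncentral t gives 40.7, so 41. At 80% power the figures are 30 and 31. Exact power at 42 per group is 90.9%. The stated 42 is thus close to the calculation for an unadjusted comparison, and design and analysis agree with each other.

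**Step 2. Effect of adjustment.** ANCOVA on the baseline score replaces the SD by 2.75 × √(1 − r²) and costs one degree of freedom (2n − 3 in place of 2n − 2). The equivalent sample size for a t test is 42 / (1 − r²). The half-width of the 95% interval is t(0.975) × residual SD × √(2/42). At r = 0.5, for example, the residual SD is 2.75 × √0.75 = 2.38, and the standard error falls from 2.75 × √(2/42) = 0.60 to 2.38 × √(2/42) = 0.52.

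All figures are for 42 per arm:

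| r | Residual SD | Variance saved | Equivalent n per arm | 95% CI half-width | Power, difference 2 | Power, difference 1.5 |
|---|---|---|---|---|---|---|
| unadjusted | 2.75 | – | 42 | 1.19 | 90.9% | 69.5% |
| 0.1 | 2.74 | 1% | 42 | 1.19 | 91.1% | 69.9% |
| 0.2 | 2.69 | 4% | 44 | 1.17 | 91.9% | 71.3% |
| 0.3 | 2.62 | 9% | 46 | 1.14 | 93.2% | 73.5% |
| 0.5 | 2.38 | 25% | 56 | 1.03 | 96.7% | 81.4% |
| 0.6 | 2.20 | 36% | 66 | 0.96 | 98.5% | 87.0% |

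**Step 3. Chance imbalance.** The baseline difference between arms has standard error 2.75 × √(2/50) = 0.55 with all 50 per arm, or 2.75 × √(2/42) = 0.60 with 42. With equal SDs the regression slope of night 6 on baseline is r, so a one-standard-error imbalance moves the unadjusted estimate by r times that amount. At r = 0.5 this is 0.5 × 0.55 = 0.28 points (50 per arm) or 0.5 × 0.60 = 0.30 points (42 per arm), which is 14% to 15% of the 2-point target.

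**The case against.** The strongest reply is that nothing here is invalid. In a 1:1 randomised trial the t test is unbiased over randomisations and keeps its type I error, and the sample size was built for that comparison. This stands: the point is about efficiency, not error. Lost precision and chance imbalance must also not be counted as two separate harms.

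The gain could also be small. Both scores are single-night ratings about six nights apart. Selection for insomnia may narrow the baseline range. The titration rule raises the dose level for patients who still report poor sleep, which could weaken the correlation further. At r = 0.1 to 0.2, power for a 2-point difference moves only from 90.9% to 91.1% or 91.9%. With all 50 per arm evaluable, unadjusted power is already 95.0%. The larger gains occur at 1.5 points, which is below the protocol's own target. All of this limits the size of the benefit, but none of it is a reason to leave the baseline out, since adjusting costs one degree of freedom.

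The text does not name the instrument used on the pre-treatment night. The EAPC questionnaire makes the same 0–10 scale very likely, but the schedule figure that would confirm it is not available. A pre-treatment diary value for total sleep time or sleep onset latency is not stated either.

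Finally, the article is condensed, its method sentence is general, and covariates are often set in an analysis plan. That carries less weight here, because a method is stated, it follows directly on the sentence about the sleep-quality scale, and no other is offered.

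**Conclusion.** The concern holds as a recommended improvement, not a correction of an invalid analysis. The stated primary comparison ignores a baseline score that the trial plans to collect. For r between 0.3 and 0.6, using it is worth the equivalent of 4 to 24 extra patients per arm on 42 (46 − 42 to 66 − 42). For r of 0.1 to 0.2 the benefit is slight. Power for the 2-point target is adequate either way; the practical gain is a narrower interval and better power if the true effect is smaller. The conclusion rests on the pre-treatment night using the same 0–10 scale, and its size rests on r, which the article does not give.

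**What to change.** Replace the t test as the primary analysis with a linear model (ANCOVA) of the night-6 sleep-quality score on treatment, with the pre-treatment-night score as covariate, and report the adjusted mean difference with its 95% confidence interval. Centre, the stratification factor, is a sensible further term; with three units it uses two more degrees of freedom. Keep the unadjusted t test as a sensitivity analysis.

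Apply the same model to the actigraphy endpoints, and to diary total sleep time and sleep onset latency where a pre-treatment value exists. State in the text that the pre-treatment night uses the same 0–10 scale as night 6.

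The cost is about one sentence of analysis wording, fixed before unblinding. The Trial status section reports recruitment as ongoing, so at that point the change could still be made. No new data, patients or change to the sample size are needed.

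### The primary and both secondary endpoints share one unadjusted 5% threshold with no testing order, so total sleep time or sleep onset latency can be declared significant after a null primary result

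*Protocol article*

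**What the plan says.** The Sample size section rests on one endpoint: "The primary variable used in the sample size calculation is patient-reported sleep quality on an NRS of 0–10 during night 6". The difference to be detected "is 2 for the primary outcome sleep quality, scored on the NRS", with an expected SD of 2.75 and a 5% significance level.

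The section Study objectives and endpoints names two secondary variables: "The secondary objective is to study the effectiveness of zopiclone on mean self-reported total sleep time and sleep onset latency". Table 1 places both at night 6, measured by sleep diary.

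The section Data collection and statistics assigns Student's t test to continuous variables and then gives the significance rule. A p value of 0.05 or less "will be considered statistically significant when comparing the two groups for the primary endpoint or the two secondary endpoints". The article states no adjustment, testing order or gate, and it does not say whether the secondary results are confirmatory or supportive.

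Table 1 also has an explorative row, again for the diary at night 6, with the objective "To study the short-time effectiveness of zopiclone on patient-reported TST, SOL, SE, WASO, and NWAK". TST and SOL therefore appear in both the secondary and the explorative part of the table.

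**The concern.** The rule is written down, so it can be judged as it stands. It names three comparisons, gives each a full 5% test and joins them with a plain "or". Nothing makes TST or SOL depend on the primary result. If the night-6 sleep quality comparison is null and SOL reaches p = 0.04, the rule as worded lets SOL be reported as a statistically significant effect of zopiclone.

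The Discussion says that the results are meant to guide treatment decisions. A significant finding on a secondary sleep variable could then carry the message of a trial that failed on its primary endpoint, and the reader would not know how likely such a finding is by chance.

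**Working it through.** **1. The plan's own figure.** Inputs from the Sample size section: difference 2, SD 2.75, level 5%, and n = 33 per group for 80% power or 42 for 90%. The article does not state sidedness.

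- Normal approximation, two-sided: n = 2 × SD² × (1.960 + z_power)² / difference².
- 80% power: 2 × 7.5625 × (1.960 + 0.842)² / 4 = 29.7, so 30 per group.
- 90% power: 2 × 7.5625 × (1.960 + 1.282)² / 4 = 39.7, so 40 per group.
- Exact t-test version: 31 and 41.
- One-sided 5%, normal approximation: 24 and 33.

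The stated 33 and 42 are within two patients of the exact two-sided figures and do not fit a one-sided level. The 5% is therefore taken as two-sided, and it belongs to one test, that of the primary endpoint.

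**2. Error of the primary endpoint alone.** One test at p ≤ 0.05 gives 5%. The rule does not change this.

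**3. Chance of at least one p ≤ 0.05 among the three when all three nulls are true.**

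- Independent tests: 1 − 0.95³ = 0.1426.
- Upper bound for any correlation: 3 × 0.05 = 0.15.
- Common correlation r between the test statistics: 1 − ∫ [Φ((1.96 − √r·x)/√(1−r)) − Φ((−1.96 − √r·x)/√(1−r))]³ φ(x) dx, evaluated numerically.

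**4. The same for the two secondaries alone**, which is the relevant case when the primary effect is real but neither secondary is affected. Independent tests: 1 − 0.95² = 0.0975. For correlated tests, use the integral above with power 2 in place of 3.

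| Assumed correlation | Any of three | Either secondary |
|---|---|---|
| 0 | 14.3% | 9.8% |
| 0.5 | 12.5% | 9.1% |
| 0.7 | 10.9% | 8.3% |
| 0.8 | 9.8% | 7.8% |
| 0.9 | 8.4% | 7.0% |

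**5. Check with t tests.** Simulated t tests on three endpoints (40,000 trials each) gave 14.3% (42 per arm) and 14.0% (50 per arm) at correlation 0, and 11.1% and 11.0% at 0.7, in agreement with the table.

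**6. Effect of a gate.** If the secondaries are tested only after a significant primary, the chance of any false positive with all three nulls true cannot exceed the 5% of the primary test. The gate alone does not deal with step 4, because once it is open two 5% tests remain. Holm across the two brings that case to at most 5%.

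**The case against.** The best defence is that this is an ordinary hierarchy. The Abstract, the objectives and the Sample size section name the same single primary endpoint, it alone drives the sample size, and TST and SOL are called secondary throughout. The "or" may simply list the comparisons to which the threshold applies. The sentence also restrains: it leaves the explorative outcomes outside the significance rule. Finally, testing order is often left to a statistical analysis plan, and one may exist that is not shown.

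Much of this stands. A reader might infer that the trial's error rate is 11% to 14% rather than 5%. The documents do not support that. They never claim 5% over three endpoints, they do not define success as significance on any one of them, and the primary conclusion keeps its 5%. The larger figures also need all three nulls to be true and an assumed correlation.

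A reader might also infer that the double listing in Table 1 leaves the status of TST and SOL contradictory. It is mostly redundancy. The text treats both as secondary each time, and the explorative row reads as the whole diary panel, parallel to the actigraphy row.

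The appeal to an unseen analysis plan does not remove the point. The article did not leave the matter open; it stated an unconditional rule. A gate set elsewhere would contradict this sentence.

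**Conclusion.** The point holds as a weakness in a written rule. The sentence allows a secondary endpoint to be declared statistically significant after a null primary, at the same unadjusted threshold as the primary.

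Its size depends on how the results are used. For the primary endpoint alone there is no inflation. If significance on any of the three counts as evidence of efficacy, the chance of a false positive is about 14% under independence, 11% at correlation 0.7 and 8% at 0.9. For the two secondaries alone it is about 10%, 8% and 7%. These figures assume two-sided tests, all relevant nulls true and a common correlation that the documents do not give. The plan's sample size and primary analysis are not affected. This is an inexpensive improvement, not an error in the main conclusion.

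**What to change.** Amend the significance sentence in Data collection and statistics along these lines: night-6 sleep quality on the NRS is tested at two-sided 5%. TST and SOL at night 6 are declared significant only if that test is significant, using Holm across the two (the smaller p value against 0.05/2 = 0.025 and, if that is met, the larger against 0.05). In all other cases they are reported as supportive estimates with confidence intervals.

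Holm is preferable to a fixed order of TST and SOL, because nothing in the documents ranks one above the other. As a tidy-up, remove diary TST and SOL from the explorative row of Table 1.

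The cost is one sentence and one table row; primary power and sample size are unchanged. Secondary results after a null primary become descriptive. Holm also lowers the power for each secondary. At worst, when the other secondary is not significant, a test with 80% power at the 5% level has about 71% at 2.5% (Φ(1.960 + 0.842 − 2.241) = Φ(0.56)). The loss is smaller when both secondaries respond. The article reports recruitment as ongoing and sets the main analysis after 100 patients, so on its timetable the change can be made before the data are analyzed.
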